### Follow-up

The start of follow-up (the index event) will be the date of the index hospital procedure (PCI, CABG) or start date of the hospital episode that contains the ACS diagnosis (ACS). Patients will be followed up until 12 months after the index event, since DAPT is prescribed for 12 months in accordance to guidelines.

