Assignment to interventions	Participants are assigned to DAPT interventions in hospital.	Participants enter the study at index procedure date for PCI and CABG, and episode start date for ACS, and will be assigned to DAPT interventions using first prescription in CPRD (within 2 months of hospitalisation) as a proxy for what they were prescribed in hospital (there are no medications data in HES). This assignment will exclude a proportion of eligible patients (those who died or experienced a major bleed that caused them to stop DAPT, or patients who have no prescription for DAPT within the 2-month window); we will identify and describe the characteristics of these excluded patients. In sensitivity analyses, we will address the robustness of results to different assumptions about the intervention group in those patients where the DAPT medication is unknown or a major bleed occurs prior to the first DAPT medication, by using multiple imputation models for handling missing data. Prior known information regarding the likely prescription based on patient characteristics or general policies will be incorporated in these analyses.
Follow-up	Starts at assignment to intervention and ends at first bleed or 12 months from assignment (whichever comes first).	Starts at time of hospitalisation for PCI, CABG or ACS and ends at first bleed or 12 months from hospitalisation (whichever comes first).
Primary outcome	Any bleed within 12 months of the start of DAPT (DAPT is prescribed at hospitalisation for PCI, CABG or ACS).	Any bleed within 12 months of hospitalisation for PCI, CABG or ACS.
Analysis	Intention to treat	According to first prescription for DAPT in CPRD

CABG, coronary artery bypass grafting; CRPD, Clinical Practice Research Datalink; DAPT, dual antiplatelet therapy; HES, Hospital Episode Statistics; PCI, percutaneous coronary intervention; PICO, Population, intervention, comparator, outcome.

In patients who have undergone PCI, estimate the effect on bleeding events of assignment to aspirin and clopidogrel (reference) versus aspirin and prasugrel or aspirin and ticagrelor.In patients who have undergone CABG, estimate the effect on bleeding events of assignment to aspirin (reference) versus aspirin and clopidogrel.In patients who are conservatively managed after presenting with ACS, estimate the effect on bleeding events of assignment to aspirin (reference) versus aspirin and clopidogrel.

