We will classify patients according to the first prescription recorded in CPRD during the first 2 months after hospitalisation for PCI, CABG or ACS. This 2-month window is based on variability in the amount of DAPT medication provided to patients in hospital following their PCI, CABG or ACS and hence variability in the time when they first request a repeat prescription from their general practice. A preliminary investigation showed that more than 75% of eligible patients have a prescription for one or more antiplatelet agents during this time period. If a patient only has a prescription for aspirin during the 2-month window after hospital discharge, they will be assigned to an aspirin only intervention. If patients also receive a prescription for clopidogrel, prasugrel or ticagrelor, they will be assigned to aspirin/clopidogrel, aspirin/prasugrel or aspirin/ticagrelor. If there is a prescription for more than one additional antiplatelet agent in the 2-month window, we will assign the patient to an intervention based on the agent prescribed first. For example, if a patient has an aspirin prescription and a prescription for clopidogrel before a prescription for ticagrelor, the patient will be assigned to the aspirin/clopidogrel intervention. Patients with no prescriptions in CPRD for aspirin, or aspirin and clopidogrel, prasugrel or ticagrelor within the 2-month window will be excluded from the main analysis. We will conduct sensitivity analyses of all eligible patients including those with unknown DAPT regimens or a major bleed prior to first DAPT prescription, by estimating assignment to DAPT interventions for those with no prescription data using multiple imputation based on a range of assumptions.^20^

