### Statistical analyses

We will describe temporal changes in DAPT prescribing and bleeding for PCI, CABG and ACS populations. We will use descriptive statistics to summarise the characteristics of the different intervention groups and standardised mean differences to compare them. We will estimate rates of bleeding (number of events/person time) with 95% CIs for each group. We will separate major and minor bleeding since adverse events of each type have different health and resource use consequences.

Analyses will estimate the effects of assigned intervention (analogous to an intention-to-treat analysis of a randomised trial) for the antiplatelet regimens corresponding to the first prescription of aspirin or DAPT in CPRD (see Interventions). We will use parametric survival models to estimate adjusted HRs with 95% CIs for the time to first bleeding event, comparing intervention groups for each target trial. Exploratory analyses, including assessment of proportional hazards assumptions, will be used to inform the choice of survival distribution (eg, Weibull). Estimated time-dependent event probabilities will be used to update existing cost-effectiveness models.^26^ The confounding factors to be included in the model (which will be identified as described previously and grouped into confounding domains from our data set), the modelling strategy and the approach to handling correlated covariates will be documented in a data analysis plan. Participants free from a bleeding event will be censored at 12 months after the index event. For secondary endpoints, we will use survival models to estimate adjusted HRs with 95% CIs for time to first event. For mortality outcomes, we will take account of the competing risks of death due to other causes.

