We will perform three sets of sensitivity analyses:We will address the unknown intervention group of eligible patients who have no prescription data and therefore cannot be assigned to an intervention (ie, those that died before receiving their first prescription, had a major bleed which caused them to stop DAPT or have no aspirin/DAPT prescription recorded in CPRD within the 2-month window). These analyses will be undertaken using multiple imputation methods to deal with missing information on DAPT medication and will take patient characteristics, procedure/diagnosis and general medication policies into account, using a range of assumptions.We will address the possibility that some minor bleeding events are not documented in CPRD but nevertheless prompt medication changes. We anticipate that most bleeding events will occur soon after the index event and before any medication change. Medication changes will be described relative to bleeding events observed (eg, before event, after event, no bleeding event observed). If a substantial proportion (>10%) of people change medication before their first bleeding event, we will perform a sensitivity analysis excluding these patients.We will assess the sensitivity of our findings when the analysis is restricted to a subpopulation of patients at low risk of bleeding (ie, excluding people at high risk for bleeding) who, we hypothesise, have the lowest risk of residual confounding.

We will attempt to identify an instrumental variable (eg, clinician/GP practice prescribing practice) to control for confounding by indication. If we are successful, we will repeat the above analyses for the PCI, CABG and ACS populations.

We will explore the consistency of treatment effect estimates in the following subgroups: ACS versus non-ACS (PCI and CABG populations); diabetic versus non-diabetic; chronic kidney disease versus non-chronic kidney disease; concurrent prescription for proton pump inhibitors versus no prescription for proton pump inhibitors. All subgroups will be defined in the data analysis plan and chosen based on the characteristics of the analysis populations before carrying out any analyses by intervention group. We will report p values from tests of interaction.

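### Follow-up starts at the index event but the arm is set by GP prescriptions over the next 2 months, so early clopidogrel bleeders in CABG and ACS can be dropped or counted as aspirin-only events

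*Protocol article*

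**What the plan says.** Table 1 sets the target trial beside its emulation. In the target trial, follow-up "Starts at assignment to intervention and ends at first bleed or 12 months from assignment (whichever comes first"). In the emulation it "Starts at time of hospitalisation for PCI, CABG or ACS and ends at first bleed or 12 months from hospitalisation (whichever comes first"). The Follow-up section confirms the second: "The start of follow-up (the index event) will be the date of the index hospital procedure (PCI, CABG"), or the start of the episode containing the diagnosis for ACS.

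The arm is observed later. Under Interventions: "We will classify patients according to the first prescription recorded in CPRD during the first 2 months after hospitalisation for PCI, CABG or ACS". A patient who "only has a prescription for aspirin during the 2-month window after hospital discharge" goes to the aspirin-only arm, and no exception is stated for a bleed inside the window. Patients with no qualifying prescription in the window are left out of the main analysis.

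Table 1 acknowledges the consequence: "This assignment will exclude a proportion of eligible patients (those who died or experienced a major bleed that caused them to stop DAPT", among others). The abstract calls the unknown arm of early bleeders the study's main limitation. Table 1 promises to describe the excluded patients, and the first sensitivity analysis under Statistical analyses plans multiple imputation for eligible patients without prescription data.

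**The concern.** Between time zero and the prescription that fixes the arm, a patient can have the primary outcome, and that outcome can change the arm or remove the patient. There are two routes.

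- **Exclusion.** A patient who bleeds and then has no qualifying prescription leaves the main analysis, and the bleed leaves with them.
- **Reclassification (CABG and ACS only).** A patient discharged on aspirin and clopidogrel bleeds, stops clopidogrel and later receives a GP aspirin prescription. Under the aspirin-only rule this bleed belongs to the reference arm.

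Reclassification takes events from the clopidogrel arm and adds them to the reference arm, so it acts in one direction: it makes adding clopidogrel look safer than it is. Exclusion lowers the absolute rates, and the estimated event probabilities are intended for the cost-effectiveness models. The protocol itself expects most bleeds soon after the index event, which is when both routes operate.

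**Working it through.** **1. The plan's own figures.** The protocol gives no figure for this bias. Its sample-size inputs are the base for what follows, and they reproduce.

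- PCI events: 6738 × 0.09 + 842 × 0.12 = 707 (with ticagrelor, 770 × 0.12 in place of the last term: 699); stated 700.
- CABG events: 2556 × 0.05 + 595 × 0.09 = 181; stated 180.
- ACS events: 8148 × 0.05 + 3082 × 0.09 = 685; stated 680.
- Detectable HR = exp[(z₀.₉₇₅ + z_power)/√(D·p(1−p)·(1−R²))]. CABG with D = 180, p = 0.8, R² = 0 gives 1.829 (90% power) and 1.685 (80%); stated 1.83 and 1.69. The other Table 2 entries also reproduce, within 2 points of power.

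**2. Reclassification in closed form (CABG, ACS).** True HR from the protocol's rates: ln(1 − 0.09)/ln(1 − 0.05) = 1.84. Let a share f of clopidogrel-arm bleeders, m = f × events, move to aspirin. The risks become (e₀ + m)/(n₀ + m) and (e₁ − m)/(n₁ − m). Example, CABG with f = 10%: m = 0.10 × 53.55 = 5.4; risks 133.2/2561.4 = 0.0520 and 48.2/589.6 = 0.0817; HR 1.60.

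| Share moved (assumed) | CABG: patients, HR | ACS: patients, HR | HR if truth is 1 (CABG / ACS) |
|---|---|---|---|
| 2% | 1, 1.79 | 6, 1.78 | 0.98 / 0.97 |
| 5% | 3, 1.72 | 14, 1.69 | 0.94 / 0.93 |
| 10% | 5, 1.60 | 28, 1.56 | 0.88 / 0.87 |
| 20% | 11, 1.37 | 55, 1.31 | 0.77 / 0.75 |

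Patient counts are for the 9% v 5% case.

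**3. Simulation, ACS numbers.** Assumed, not in the documents: first GP prescription uniform over days 0–40; 16% (flat), 30% or 50% of the 12-month hazard in the first 60 days; up to half of pre-prescription clopidogrel bleeders moved; up to half of pre-prescription bleeders excluded.

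| Hazard in first 60 days | Moved | Excluded | True HR | Index-date HR |
|---|---|---|---|---|
| 30% | 25% | 0 | 1.83 | 1.76 |
| 30% | 50% | 0 | 1.87 | 1.70 |
| 50% | 25% | 0 | 1.84 | 1.71 |
| 50% | 50% | 25% | 1.87 | 1.60 |
| 50% | 0 | 50% | 1.83 | 1.83 |

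With flat hazard and 25% moved, the loss is about 0.03; the largest loss is 0.27. True values vary around 1.84 through Monte Carlo error of a few hundredths. The last row shows that exclusion at the same rate in both arms leaves the HR alone. Starting at day 60 among event-free patients returned the true post-day-60 HR in every scenario. The heaviest scenario moves about 25 of 277 clopidogrel bleeders (9%), so the 20% row in step 2 lies outside this range.

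**4. PCI.** With 9% v 12% and half of early bleeders lost (assumed), rates per 100 person-years fall from 9.68 to 8.87 and from 13.07 to 11.96, about 8% each. The rate ratio goes from 13.07/9.68 = 1.350 to 11.96/8.87 = 1.348. In a separate simulation the HR was unchanged when prescription timing and exclusion matched across arms. With mean times of 15 v 25 days it ranged from 1.28 to 1.37 against a true value of about 1.36.

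**5. What the imputation covers.** Table 1 speaks of unknown medication or a major bleed before the first DAPT medication. Interventions repeats this but ends by imputing for those with no prescription data, and the first sensitivity analysis is defined the same way. A patient moved to aspirin-only has prescription data. The broader Table 1 wording names major bleeds only, whereas the primary outcome is any BARC type 2–5 bleed.

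**The case against.** The strongest reply is that the plan already knows this. It names the limitation, will describe the excluded patients and plans an all-eligible imputation analysis. Regimens start in hospital, so the index date is close to true treatment start, and the GP prescription is a proxy that GPs are said rarely to alter. On that view the problem is exposure measured with error, not a wrong time zero. Much of this stands. But Table 1 itself concedes that a bleed can stop DAPT before the prescription, so the proxy fails in exactly the patients who matter, and a sensitivity analysis does not protect the main estimate.

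Some stronger readings are tempting and not supported.

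- *Immortal time biases all three HRs.* Pre-prescription time is fully immortal only for death. A bleed in that time counts if a qualifying prescription follows. For PCI the HR barely moves (step 4).
- *The bias is known to be large.* The stopping shares are assumed. The only discontinuation figure in the text is 11%, from one nuisance-bleeding study and an imperfect comparator. Applied to an assumed 18% of bleeds before the prescription, it moves about 2% of bleeders, the first row of step 2.
- *The imputation model wrongly omits the outcome.* The protocol says the imputation "will take patient characteristics, procedure/diagnosis and general medication policies into account". That is a summary, and an article may leave the predictor list to the data analysis plan.
- *The arm rule contradicts itself.* Statistical analyses refers to "antiplatelet regimens corresponding to the first prescription of aspirin or DAPT in CPRD", but it points back to Interventions, where the operating rule is given.
- *Index-stay bleeds distort the result.* The code lists are in an appendix that is not shown, so this cannot be judged.

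Replacing the main HR with a 2-month landmark would also be costly, as set out under the fix.

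**Conclusion.** The concern holds in limited form. As written, the main analysis lets events after time zero decide entry and arm. In CABG and ACS the reclassification route lowers the clopidogrel HR, and the planned imputation does not clearly cover it. In PCI the effect is mainly on absolute rates. Mortality outcomes carry fully immortal time up to the prescription.

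The direction in CABG and ACS follows from the protocol's rules, provided some early bleeders stop clopidogrel and are later prescribed aspirin. The size does not follow from the documents: under the assumptions in step 3 a true HR of 1.84 falls by about 0.03 to 0.27. Given the disclosure and the planned sensitivity analysis, this should be fixed but does not invalidate the design.

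**What to change.** 1. **Add an analysis aligned with assignment**, pre-specified beside the index-date HR in all three target trials. Use either delayed entry at the first qualifying prescription with a short grace period (time at risk starting once the arm is settled) or a 2-month landmark with the present arm rule. Report bleeds and deaths before that point descriptively. Do not interpret the index-date CABG and ACS HRs without it.
2. **Extend the all-eligible imputation analysis** to patients with any bleed before a second-agent prescription, including those with only aspirin recorded. State that the imputation model contains the bleed/death indicator and its time (cumulative hazard).
3. **Use one anchor for the 2-month window.** Interventions uses both hospitalisation and discharge; Table 1 uses hospitalisation and the abstract discharge.

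The cost is wording and code; no new data are needed. The aligned analysis drops early bleeds and answers a narrower question, about patients still event-free when the arm is known. Under an assumed Weibull shape of 0.6, a 60-day landmark loses (60/365)^0.6 = 34% of events. CABG events fall from 180 to about 119, and the detectable HR rises to exp[3.2415/√(119 × 0.16)] ≈ 2.10 at 90% power, from 1.83. Delayed entry keeps more events but may misclassify patients whose aspirin and clopidogrel prescriptions fall on different dates, which is why a grace period is needed. For these reasons the aligned analysis should accompany the index-date analysis, not replace it.

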### Confounding and cointerventions

Potential confounders (variables that predict both risk of bleeding and intervention group) will be specified a priori.^22 23^ We will identify confounders and cointerventions using literature review and clinician expertise as recommended by the Cochrane Bias and Non-Randomised Studies Methods Groups.^17^ We will carry out a comprehensive and systematic literature search to identify all RCT and cohort studies of DAPT interventions, or cohort studies that identify predictors of bleeding. The literature searches for the review are included in supplementary appendix 2. Abstracts will be screened by one researcher and full-text papers will be obtained. Data on confounders and cointerventions will be extracted by two researchers independently using a data extraction form specifically designed for the study; variables extracted will include study characteristics, population characteristics (reported in the tables of baseline characteristics), factors adjusted for in the statistical analyses and factors reported to predict risk of bleeding in our populations. We will not perform a risk of bias assessment because the aim of the review is only descriptive (ie, the output will be lists of confounders and cointerventions) and there are no established criteria for assessing the validity with which primary researchers consider potential confounders and cointerventions; therefore, it would be inappropriate to apply a risk-of-bias tool for studies estimating a treatment effect. We will use ‘saturation’ as a criterion for discontinuing data collection, defined as review of 10 consecutive studies without identifying an additional confounder/cointervention.

10.1136/bmjopen-2019-029388.supp2Supplementary file 2

In parallel, we will conduct semiquantitative interviews with six clinicians in each of three groups: cardiologists; cardiac surgeons and GPs (to determine whether DAPT prescriptions are changed in primary care). The main aim of the clinician interviews is to understand DAPT prescribing practice in the UK and identify the factors (relating to patients, centres and prescribing practices of the individual doctors) that influence the decision about which antiplatelet regimen to prescribe. All factors that influence DAPT prescribing (confounders) identified from the literature review and clinician interviews will be combined in a short survey (SurveyMonkey). The survey questionnaire will be administered online to all consultant members of the British Cardiovascular Society (cardiologists) and the Society for Cardiothoracic Surgery (cardiac surgeons). The survey will be either emailed to all members individually (if the professional bodies agree) or advertised in weekly/monthly newsletters. Confounders will be grouped in confounding domains.^17^ We will attempt to identify each potential confounder (identified through the literature review, clinician interviews and survey) in the CPRD or HES data set but acknowledge that there may be missing data across patients (and time) for some confounders.

### Sample size

Estimated rates of bleeding with the different therapies are 5% for aspirin, 9% for aspirin/clopidogrel and 12% for aspirin/prasugrel and aspirin/ticagrelor.^5 6 24 25^ Preliminary feasibility counts provided by CPRD suggest that there will at least the following numbers of patients eligible for each target trial:PCI: aspirin/clopidogrel (reference, 6738 patients) versus aspirin/prasugrel (842 patients) or aspirin/ticagrelor (770 patients)CABG: aspirin (reference, 2556 patients) versus aspirin/clopidogrel (595 patients)Conservatively managed ACS: aspirin (reference, 8148 patients) versus aspirin/clopidogrel (3082 patients)

These estimates give expected event rates of at least 700 for PCI, 180 for CABG and 680 for ACS, assuming a ratio of 8:1 (aspirin/clopidogrel:aspirin/prasugrel or aspirin/clopidogrel:aspirin/ticagrelor) for PCI, 4:1 (aspirin:aspirin/clopidogrel) for CABG and 2.5:1 (aspirin:aspirin/clopidogrel) for ACS. The HR detectable with 90% and 80% power at the 5% statistical significance, assuming the group ratios given above, are shown in table 2. The correlation of the DAPT with other covariates adjusted for is unknown and we assessed the impact of a range of correlations (0, 0.3 and 0.5).

**Table 2 T2:** HR for a range of correlations for percutaneous coronary intervention (PCI), coronary artery bypass grafting (CABG) and acute coronary syndrome (ACS)

Ratio of presence: absence of covariate	Squared correlation with other covariates	HR detectable	
		90% power	80% power
PCI			
8:1	0 (ie, unadjusted)	1.48	1.41
	0.3	1.60	1.50
	0.5	1.74	1.62
CABG			
4:1	0 (ie, unadjusted)	1.83	1.69
	0.3	2.06	1.87
	0.5	2.35	2.10
Conservatively managed ACS			
2.5:1	0 (ie, unadjusted)	1.32	1.27
	0.3	1.39	1.33
	0.5	1.48	1.40

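### The ACS rows of Table 2 use 680 events, a count that needs 5% v 9% bleeding; with aspirin at the stated 5%, the tabled HRs yield 602 to 633 events and slightly less than the stated power

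*Protocol article*

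**What the plan says.** All inputs are in the Sample size section of the protocol article. The assumed bleeding risks are: "Estimated rates of bleeding with the different therapies are 5% for aspirin, 9% for aspirin/clopidogrel and 12% for aspirin/prasugrel and aspirin/ticagrelor". The ACS cohort is: "Conservatively managed ACS: aspirin (reference, 8148 patients) versus aspirin/clopidogrel (3082 patients"), and these numbers are presented as minimums. The event totals follow: "These estimates give expected event rates of at least 700 for PCI, 180 for CABG and 680 for ACS". The allocation assumed for this cohort is "2.5:1 (aspirin:aspirin/clopidogrel) for ACS".

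Table 2 is introduced with: "The HR detectable with 90% and 80% power at the 5% statistical significance, assuming the group ratios given above, are shown in table 2". It gives each HR at three values (0, 0.3, 0.5) of the squared correlation between treatment and the other covariates (R2 below). The ACS entries for 80%/90% power are 1.27/1.32 (R2 = 0), 1.33/1.39 (R2 = 0.3) and 1.40/1.48 (R2 = 0.5).

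The Statistical analyses section censors patients without a bleed at 12 months and commits to adjusted HRs with 95% CIs.

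**The concern.** An event total computed from 5% and 9% already contains an effect size. Table 2 then asks which HR that total can detect, and for ACS the answers are far below the effect that produced the total. If the true HR is 1.27 and aspirin patients bleed at 5%, aspirin/clopidogrel patients bleed at about 6.3%, not 9%, and there are fewer events than the table uses.

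An event-driven trial could wait until 680 events had occurred. This is a database cohort with fixed 12-month follow-up, so its event count depends on the HR. What is at stake is the accuracy of the planning table: the sensitivity it claims for the largest aspirin v aspirin/clopidogrel comparison is a little too favourable on the plan's own inputs.

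**Working it through.** **Inputs (Sample size section).** Aspirin 5%, aspirin/clopidogrel 9%; 8148 and 3082 ACS patients; 680 events; ratio 2.5:1; 5% significance; 80% and 90% power; R2 = 0, 0.3, 0.5. Sidedness is not stated. Two-sided is inferred, because one-sided gives 1.24/1.28 at R2 = 0 and does not match the table.

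**Step 1: the plan's event count.** 8148 x 0.05 + 3082 x 0.09 = 407.4 + 277.4 = 684.8, which agrees with a stated minimum of 680. Under proportional hazards, 5% v 9% means HR = ln(0.91)/ln(0.95) = 1.84.

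**Step 2: the plan's detectable HRs.** HR = exp[(1.960 + z_power)/sqrt(D p(1-p)(1-R2))], with D = 680 and p = 1/3.5, so p(1-p) = 0.2041. For 80%/90% power this gives 1.268/1.317, 1.329/1.389 and 1.400/1.476. All six printed ACS values are reproduced, so 680 was used throughout.

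**Step 3: events at each printed HR, aspirin held at 5%.** The aspirin/clopidogrel risk is 1 - 0.95^HR, and D = 8148 x 0.05 + 3082 x (1 - 0.95^HR). At HR 1.27 the risk is 6.31% and D = 407.4 + 194.4 = 601.8.

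**Step 4: power with those events.** Power = Phi[ln(HR) x sqrt(D p(1-p)(1-R2)) - 1.960]. At HR 1.27, R2 = 0 and 2.5:1: 0.2390 x sqrt(601.8 x 0.2041) = 2.649; 2.649 - 1.960 = 0.689; power 75.5%. The actual ratio is 8148/3082 = 2.64:1, so p = 0.2744 and p(1-p) = 0.1991.

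| R2 | Stated power | Printed HR | Events | Power at 2.5:1 | Power at 2.64:1 | Self-consistent HR at 2.64:1 |
|---|---|---|---|---|---|---|
| 0 | 80% | 1.27 | 602 | 75.5% | 74.4% | 1.29 |
| 0 | 90% | 1.32 | 609 | 87.2% | 86.4% | 1.34 |
| 0.3 | 80% | 1.33 | 611 | 75.9% | 74.9% | 1.35 |
| 0.3 | 90% | 1.39 | 619 | 87.2% | 86.4% | 1.42 |
| 0.5 | 80% | 1.40 | 621 | 76.4% | 75.4% | 1.43 |
| 0.5 | 90% | 1.48 | 633 | 88.3% | 87.5% | 1.50 |

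The event count is the main driver. Keeping 680 events and changing only the ratio to 2.64:1 leaves the 80% column at 79.1% to 79.4%.

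**Step 5: check without the formula.** A log-rank simulation of the R2 = 0 case (exponential times, 12-month censoring, actual group sizes, 4000 replicates) gave 601.9 events and 76.8% power at HR 1.27, and 609.0 events and 88.6% power at HR 1.32. The formula is therefore slightly pessimistic here.

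**Step 6: what would close the gap.** The aspirin rate that gives 680 events is 5.65% at HR 1.27, 5.58% at 1.32, 5.48% at 1.40 and 5.38% at 1.48. Alternatively, at 5% and HR 1.27, the cohort would need 680/601.8 = 1.13 times as many patients.

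**Step 7: the other cohorts.** The same check at the plan's own ratios leaves PCI above its stated power in every cell, because its tabled HRs exceed the HR implied by 9% v 12% (ln 0.88/ln 0.91 = 1.36). The lowest CABG figure is 79.8% against 80%. The problem is confined to ACS.

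**The case against.** The strongest reply is that the plan never says the aspirin rate stays at 5% while the HR varies. In the usual formula the event count is simply an input. If the pooled rate were fixed, 680 would stand. If aspirin/clopidogrel were fixed at 9% instead, events would be about 780 to 861 and power about 86% to 95%. This stands to the extent that the shortfall is conditional and must be stated so. It does not remove the point: aspirin is the labelled reference with a stated 5%, and both alternatives need an aspirin rate above that figure.

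A second reply is that 5% may be too low. The Introduction expects real-world bleeding to exceed what trials reported, the primary outcome includes bleeds recorded in primary care, and the patient numbers are minimums. This also stands in part. Less than one percentage point on the aspirin rate closes the gap, but the plan states no higher rate or larger cohort.

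A third reply is that nothing practical depends on it. The HRs move by 0.02 to 0.03, while Table 2 already spans 1.27 to 1.40 (80% power) and 1.32 to 1.48 (90% power) across the unknown R2. That is fair, and it limits the point to a correction of the table.

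A reader might go further and infer that a null ACS result would be taken to exclude smaller effects than the data can. The documents do not support this. The Statistical analyses section commits to 95% CIs, which show what a null result excludes, and no section uses Table 2 to interpret results.

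**Conclusion.** The point holds as a small, conditional inconsistency. The 680 ACS events belong to 5% v 9% (HR about 1.84), not to the HRs of 1.27 to 1.48 beside which they are used. With aspirin at 5%, the stated 80% power is about 75% to 77% (75.5% to 76.4% by the formula that reproduces Table 2 at 2.5:1; about 77% by simulation at R2 = 0). The stated 90% is about 87% to 89%. The rounded ratio costs about one further point by formula.

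This rests on aspirin bleeding at exactly 5%, proportional hazards, a two-sided 5% test and the stated minimum group sizes. A reader might infer that the ACS comparison is underpowered for the effect the plan expects. It is not: at 5% v 9% the formula gives power above 99% even at R2 = 0.5. The consequence is a planning table whose smallest detectable HRs are 0.02 to 0.03 too low.

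**What to change.** Recompute the six ACS cells with the event count tied to each HR, D = 8148 x 5% + 3082 x (1 - 0.95^HR), at the actual 2.64:1 ratio. The detectable HRs for 80%/90% power become about 1.29/1.34 (R2 = 0), 1.35/1.42 (R2 = 0.3) and 1.43/1.50 (R2 = 0.5). Reword the sentence on event totals so that 680 is the ACS count expected under 5% v 9%, not a minimum at every HR.

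If the sponsor expects more than 5% bleeding on aspirin, or more patients than the feasibility counts, stating that figure and computing from it would serve equally well.

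The cost is six table cells and one sentence. No patients, data or analyses change; the stated detectable HRs become slightly less favourable.
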